## Introduction

### Background

Historically, palliative care (PC) focused largely on patients with cancer. However, as the number of deaths attributed to non-cancer causes exceed cancer-related deaths [1] with patients experiencing similar distressing symptoms negatively affecting their quality of life [2,3], there is a growing realization of the importance of extending PC to non-cancer conditions.

PC provided to terminally ill non-cancer patients has been found to be effective in reducing acute care utilization [4] and improving quality of life. Nevertheless, compared to those with cancer, utilization of PC among patients with non-cancer diseases is much lower and later in their disease trajectory [3,5]. Uncertainty caused by unpredictable illness trajectory and low accuracy in the prognostication of non-cancer conditions are key barriers [6]. Lack of knowledge regarding the needs of end-stage non-cancer patients and their families and limited PC training for healthcare professionals are also associated with low use of and late referral to PC [3]. As non-cancer patients often outlive their prognosis and end up needing PC for an extended period of time, longer term sustainability is a concern [5]. Many specialist PC services are hesitant to take in such cases, resulting in high numbers of unmet needs.

Similar to other developed countries, there is a growing need for PC for a range of life limiting illnesses in Singapore [7]. Disproportionately higher deaths attributed to non-cancer causes highlight the need for PC beyond those with cancers [8]. Thus, enhancement in the provision of PC is prioritized at the national level [9]. Provision of home-based PC increases the chance of dying at home [10,11], improves symptom control [11] and quality of life [12], reduces hospital utilization [12,13] and healthcare cost in non-cancer conditions.

Traditionally, in Singapore, PC is provided to patients suffering (Ministry of Health Singapore, n.d.) from cancers in hospitals, hospices and at home [14,15] and significantly lower proportion of individuals with non-cancer conditions were referred and received home PC (unpublished data). As studies [16,17] have consistently demonstrated that non-cancer patients have similar, if not more, needs that may benefit from PC, this highlights an apparent service gap.

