As of May 2022, majority of referrals came from CGH and SACH, with other organizations contributing only 7.5% of total referrals. Patients are identified in the inpatient, specialist clinic and home setting based on a pre-determined selection criterion. Pre-assessment by the PC team of the organizations is not required. In brief, the referral criterion includes (i) dementia (at least FAST 7), (ii) Chronic Obstructive Pulmonary Disease GOLD D, irreversible chronic lung diseases, (iii) heart failure (NYHA III or IV), or (iv) renal failure (eGFR <10 ml/min per 1.73 m^2^, not for dialysis) with prognosis of <12 months. Other forms of frailty, e.g. stroke or neurodegenerative illnesses, with prognosis <6 months are also accepted. This admission criterion is based on guidance laid down by Ministry of Health and Central Provident Fund Board who oversees the use of Medisave, a national medical savings scheme. Patients who do not fall within these criteria but assessed to have PC needs are discussed on an ad-hoc basis with ViP. Referrals are vetted by ViP doctors and suitable referrals are contacted and an assessment visit date is scheduled. Patients are enrolled into the program once the service agreement is signed. Figure 1 describes the recruitment process of ViP.

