#### Data Collection

Context, mechanisms and relationships between context and outcomes, as defined in phase 1, will be tested through interviews with healthcare providers and users. As suggested by Manzano [29], questions to be asked in these interviews aim to ascertained how the program works, for whom, in what circumstances and how implementation has veered from what was initially planned. A purposive sample of 15 healthcare providers/managers and 15 healthcare users (patient and/or carers) per disease condition will be invited to take part in face-to-face or virtual interviews. The eventual sample size will be determined based on thematic saturation of the study. Data saturation is reached when the ability to obtain additional new information has been attained, and when further coding is no longer feasible [30].

In ensuring the quality of data collected, an interview guide will be used and interviewers will routinely reflect on interview experience and discuss data as they are being collected. Based on emerging understanding and identification of key knowledge gaps throughout the process of interviewing, interview questions will be revised accordingly.

Healthcare services utilization, health outcomes, healthcare cost and caregiver burden data will be collected and analyzed over time to evaluate intervention outcomes of ViP. A quasi-experimental design will be adopted by comparing the outcomes of the intervention group against a comparator group for healthcare utilization, outcomes and cost. Due to limited data available, a pre-post comparison will be made for caregiver burden. A quasi-experimental design is selected as it more truly mimics real-world constraints and provide a balance between internal and external validity [31]. Pragmatically, all patients who agree to participate, are accepted into the home-based PC service, utilized the services for at least one month and passed away as of December 2022 will be included as the intervention group. A retrospective comparator group will be identified from available CGH and SACH clinical databases. We plan to restrict the databases to within CGH and SACH for the identification of comparators. This is because patients are planned to be recruited from CGH and SACH in the first 2 years. This is a way of ensuring comparability between intervention and comparator group while keeping the data manageable.

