In identifying retrospective comparator group, relevant databases will initially be filtered for individuals who were referred to home hospice services between 2016–2019, have completed their advance care planning (ACP) and have died as of December 2020. Death status will be obtained from National Registry of Diseases Office records. Then, using a propensity matching strategy, a comparator group matched to intervention group in terms of age, gender, ethnicity, functional status, clinical status and re-admission characteristics will be identified. A ratio of 1:1 of intervention to comparator group will be used for matching.

In the assessment of healthcare utilization and health outcomes, date of death will be used as reference point for comparison. Acute hospital utilization (emergency department (ED) attendances, inpatient admissions, intensive care unit (ICU) admissions and length of stay (LOS)) will be extracted backwards from the date of death for 1 month (30 days), 3 months (90 days) and 6 months (180 days). Concordance of actualized place of death with preferences discussed as part of ACP will be determined after death as described by Tan et al [32].

We take a healthcare system perspective in examining the effect of ViP on healthcare cost. Development costs, program implementation costs and healthcare utilization costs will be measured. Development costs include costs incurred during the development of ViP. The program implementation costs consider costs related to the implementation of the program including the manpower, travel, equipment, materials used for patient and caregiver training and costs associated with multidisciplinary team meetings. The development and implementation costs will be systematically collected using the WHO’s CostIt instrument [33] and will be divided by the number of clients enrolled into the program to obtain per patient cost. Healthcare utilization cost for the use of hospital inpatient and outpatient services and primary care services in the metrics of full gross bill amounts will be extracted for six-month period before death.

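### Apart from completed advance care planning and death, comparators need only a home hospice referral, while ViP patients must be accepted and use the service for at least one month

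*Protocol article*

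**What the plan says.** Both entry rules are in the protocol article, under Data Collection (Phase 2).

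- **ViP group.** It consists of "all patients who agree to participate, are accepted into the home-based PC service, utilized the services for at least one month and passed away"; the cut-off for death is December 2022. The section on the Violet Program describes the steps before that. On screening it says: "Referrals are vetted by ViP doctors and suitable referrals are contacted and an assessment visit date is scheduled". On the final step before a patient counts as enrolled it adds: "Patients are enrolled into the program once the service agreement is signed".
- **Comparator group.** The article states that "relevant databases will initially be filtered for individuals who were referred to home hospice services"; the referral years are 2016 to 2019. These individuals must also "have completed their advance care planning (ACP) and have died as of December 2020". Propensity matching at 1:1 follows, on demographics (age, gender, ethnicity), functional and clinical status, and re-admission history.

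Acute utilization is then counted back from death over 30, 90 and 180 days, and utilization cost over six months. The Background remarks of non-cancer patients: "Many specialist PC services are hesitant to take in such cases, resulting in high numbers of unmet needs".

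**The concern.** The two groups are selected at different points on the care pathway. A ViP patient has passed vetting, an assessment visit, a signed agreement, consent to participate and a month of use. A comparator has been referred, but need not have been accepted, have agreed to home care or have received any.

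Whether a provider takes a patient on, and whether the family wants care at home, may bear on hospital use near death. If so, part of any difference between the groups reflects who gets into a service and not what ViP does. The reference is also undefined: the comparators are an unknown mixture of patients who received home hospice, were turned away, or declined. This is the article's only controlled comparison for the research question on how far ViP achieves its intended outcomes, since caregiver burden is assessed pre-post. The problem is separate from any difference in survival time after entry and would remain if that were equalised.

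**Working it through.** **Step 1. The entry rules side by side**

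| Condition | ViP group | Comparator group |
|---|---|---|
| Referral | Yes | Yes, to home hospice, 2016–2019 |
| Vetted and accepted by the service | Yes | Not stated |
| Agreement signed or care agreed to | Yes | Not stated |
| Minimum use of the service | One month | Not stated |
| Completed ACP | Not stated as an entry condition; Table 2 measures it as a percentage of enrolled patients | Yes |
| Death | As of December 2022 | As of December 2020 |

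Two mismatches follow. Uptake is required of ViP patients only. Completed ACP is required of comparators only.

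**Step 2. Does anything planned remove the uptake mismatch?**

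- The matching variables do not measure acceptance, willingness to be cared for at home, or receipt of care.
- Restricting the search to CGH and SACH databases aligns the institutions, not the point of entry.
- The selection-bias check under Strengths and Limitations compares participants with decliners on demographics and, for providers, role. It does not concern how comparators enter.
- Data Analysis promises a sensitivity analysis without saying of what.

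**Step 3. Size (illustration only)**

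The article gives no event rate, effect size or sample size for this comparison, so there is no figure to reproduce. Let *f* be the share of comparators who never received home care, and *r* their acute-use rate relative to comparators who did. Neither is in the documents; both are assumed. If ViP performs exactly like received home hospice, the expected rate ratio (ViP over comparator) is

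RR = 1 / (1 − f + f·r)

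| f | r = 0.8 | r = 1.0 | r = 1.2 | r = 1.5 | r = 2.0 |
|---|---|---|---|---|---|
| 0.1 | 1.02 | 1.00 | 0.98 | 0.95 | 0.91 |
| 0.2 | 1.04 | 1.00 | 0.96 | 0.91 | 0.83 |
| 0.3 | 1.06 | 1.00 | 0.94 | 0.87 | 0.77 |
| 0.5 | 1.11 | 1.00 | 0.91 | 0.80 | 0.67 |

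For example, f = 0.2 and r = 1.5 give 1 / (0.8 + 0.3) = 1 / 1.10 = 0.91. With f = 0.5 and r = 0.8 the result is 1 / (0.5 + 0.4) = 1 / 0.90 = 1.11.

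An apparent benefit, no bias and an apparent harm are all possible, depending on *r*. If entry requires receipt in both groups, f = 0 and the ratio returns to 1. The formula leaves out the ACP mismatch, for which the documents offer nothing to quantify.

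**The case against.** Several counter-arguments have weight.

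- **A reader might infer that comparators enter on a referral alone.** They do not: the same sentence requires completed ACP and death. ACP records care preferences, so comparators pass a test of engagement that is not stated for ViP patients, and this could lower their acute use. This stands. But neither extra filter concerns uptake of home care, so the uptake mismatch remains.
- **A reader might infer that the bias must favour ViP.** The documents do not support that. Nothing in them says that patients turned away or declining use hospital more, and the matching on functional status, clinical status and re-admissions may absorb part of any difference.
- **A reader might expect a spurious gain in home deaths.** The stated outcome is concordance between preference and actual place of death. A patient who preferred hospital and died there counts as concordant.
- **The Background remark on hesitant services is general.** It gives no rejection rate for referred CGH or SACH patients with completed ACP. It makes a gap between referral and receipt plausible and no more.
- **Usual care after referral is a legitimate reference** for a programme meant to fill a service gap. That is fair, but the ViP side would then also have to start at referral, and the stated rule does not do this.
- **The article condenses a fuller protocol**, and the filter is described as an initial one. Further criteria may exist. Even so, the article does state the two entry rules, and as stated they do not match.

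**Conclusion.** The concern holds in a limited form. Following the stated rules compares patients selected on acceptance and use with patients selected on referral, completed ACP and death. The ViP effect on acute utilization, health outcomes and cost is confounded by selection into service, and it is unclear whether the reference is received home hospice or usual care after referral.

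Neither direction nor size can be settled from the documents. The range of 0.67 to 1.11 under no true effect depends wholly on assumed values of *f* and *r*, and the bias vanishes if non-recipients use hospital as much as recipients do. The ACP mismatch could partly offset it. The conclusion assumes that no unpublished criterion requires comparators to have received home hospice care. The point should be corrected before the comparator extraction, but the documents do not show that it would overturn the result.

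**What to change.** Apply the same entry condition to both groups, and name the contrast.

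1. **Where home hospice acceptance or enrolment is recorded**, require it of comparators, with the same minimum time in service as for ViP. Report referred-but-not-enrolled comparators separately. The contrast is then ViP against received home hospice.
2. **Where it is not recorded**, name the contrast as usual care after referral. At least as a sensitivity analysis, define the ViP group at referral, enrolled or not, from the referral records behind the programme acceptance rate in Table 2, subject to approval to use those data.

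In either case, treat ACP completion alike in both groups, or state why it is required of comparators only.

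The first option costs an added filter and a smaller comparator pool. It depends on acceptance or enrolment being held in the CGH, SACH or eHints data, which the article does not say. The second dilutes the ViP contrast and needs outcome data on referred patients who never enrolled, whom the present rule excludes.

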### The Intervention: Violet Program

The Violet Program (ViP) was developed as a collaboration between Changi General Hospital (CGH) and St. Andrew’s Community Hospital (SACH) to provide home-based PC to non-cancer patients residing in the Eastern region of Singapore. VIP aims to (i) reduce unnecessary acute hospital utilization (ii) improve health outcomes (iii) reduce caregiver burden through caregiver support (iv) honour patient preferences better through integrated care while (v) keeping healthcare cost affordable.

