## Data Analysis

Interviews will be transcribed verbatim and each transcript will be checked against recordings for accuracy. Interview transcripts and observation notes will be coded using NVivo. Interviews conducted in languages other than English will be translated and transcribed in English. Like phase 1, interview transcripts will be coded and analyzed by 2 evaluators using NVivo as suggested by Gilmore et al [28]. To ensure the rigor of data analysis, regular meetings will be planned among evaluators to discuss the emerging themes identified in the data. In addition, re-analysis of qualitative data will be conducted if discrepancy is identified. An objective third person will be called in if the discrepancy cannot be resolved between the two evaluators.

Quantitative data analysis will be conducted using STATA. First, univariate analysis will be conducted using chi-square for categorical variables and t-test/ANOVA for continuous variables. Then, to estimate the effect of the program on the outcome of interest, multivariable regression analysis (Poisson or Negative Binominal regression) will be used for count data and generalized linear models will be used for continuous data. For dichotomous outcome variables, logistic regression will be used. Subgroup analysis may be conducted by patients’ primary conditions to allow for the detection of differential effects of ViP on various disease groups. To ensure robustness of the analysis, sensitivity analysis will also be performed.

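### The comparator filter does not exclude cancer and primary diagnosis is not a named matching variable, so non-cancer ViP patients may be compared with cancer patients

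*Protocol article*

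**What the plan says.** The section on the intervention describes ViP as set up "to provide home-based PC to non-cancer patients residing in the Eastern region of Singapore". Its referral criteria are disease-specific: advanced dementia, chronic lung disease, heart failure, renal failure not for dialysis, and other frailty such as stroke or neurodegenerative illness. Patients outside these criteria who have palliative needs can be discussed ad hoc.

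The intervention group for the quasi-experimental comparison is drawn from this population: patients who were accepted, used the service for at least one month and had died as of December 2022. For the comparators, Data Collection says that "relevant databases will initially be filtered for individuals who were referred to home hospice services between 2016–2019". It adds two further conditions, completed advance care planning and death as of December 2020, and limits the search to CGH and SACH databases. A 1:1 comparator group is then to be "matched to intervention group in terms of age, gender, ethnicity, functional status, clinical status and re-admission characteristics" by a propensity method.

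On the analysis side, Data Analysis plans multivariable regression without listing covariates, and states that "Subgroup analysis may be conducted by patients’ primary conditions".

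**The concern.** The characteristic that defines the programme's population, a non-cancer life-limiting illness, appears in neither the comparator filter nor the matching list. The filter instead selects on home hospice referral in 2016–2019, before ViP took its first patient in December 2020. The Background describes palliative care in that setting as traditionally given to cancer patients and says that a "significantly lower proportion of individuals with non-cancer conditions were referred and received home PC".

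The same comparator group supports all the controlled estimates: emergency attendances, admissions, intensive care use, length of stay, cost, and concordance of place of death with preference. If it contains cancer patients, a difference between the arms may reflect disease rather than ViP. The Background itself argues that needs, goals and care experiences differ enough that cancer-based models do not carry over and that distinct disease groups need tailored programmes. On that reasoning, a cancer patient is a poor stand-in for what would have happened to a ViP patient without ViP.

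**Working it through.** The article gives no sample size, diagnosis mix or expected effect for this comparison, so there is no figure to reproduce. The check sets side by side the places that define the two groups.

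1. **ViP arm** (The Intervention: Violet Program). Restricted by disease: non-cancer, with named condition groups and an ad-hoc route.
2. **Comparator pool** (Data Collection). Restricted by type of referral, period, advance care planning, death and institution. Not restricted by disease.
3. **Matching variables** (Data Collection). Age, gender, ethnicity, functional status, clinical status and re-admission characteristics. Diagnosis is not named, and clinical status is not defined.
4. **Outcome model** (Data Analysis). Regression with unspecified covariates. Primary condition appears only as a possible subgroup variable.
5. **Likely source of the pool** (Background). A service with a cancer tradition. No percentage is given.

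Steps 2 to 4 contain nothing that keeps a cancer decedent out of the comparator group. Step 5 makes it likely that such patients are in the pool.

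**Direction of the bias.** Let *c* be the share of matched comparators whose primary condition is cancer. Let *r* be the ratio of mean utilisation in cancer decedents to that in otherwise similar non-cancer decedents, and *m* the non-cancer mean. If ViP has no effect:

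- ViP mean = *m*
- comparator mean = *m*(1 − *c* + *cr*)
- apparent ratio, ViP to comparator = 1 / (1 − *c* + *cr*)

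With *c* above 0, the ratio falls below 1 when *r* is above 1 (ViP appears to reduce use) and rises above 1 when *r* is below 1 (ViP appears to increase use). It equals 1 for any *r* when *c* = 0, which is what a diagnosis restriction achieves. For concordance the same reasoning gives a spurious difference of *c* times the non-cancer proportion minus the cancer proportion. The documents give neither *c* nor *r*, so the calculation stops at the sign.

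**Subgroups.** A comparator with cancer belongs to no ViP condition group, so an analysis by primary condition would break that pair. Pairs of two non-cancer patients may also cross condition groups, because a propensity score balances covariates across the arms and does not make partners alike on each one.

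**The case against.** The strongest reply is that clinical status may be meant to include primary disease. If the propensity model did contain a cancer indicator, and no ViP patient has cancer as primary condition, cancer patients would receive a fitted score at or near zero and would largely drop out of the match. The word that introduces the filter as an initial step also leaves room for a later restriction. The article is a condensed account, the authors evidently expect to hold primary condition as a variable, and regression and sensitivity analyses are planned after matching. Balance on average is also all that any propensity match promises, so exact matching is one acceptable choice among several.

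Part of this stands. The full protocol may close the gap, and the composition of the matched group is unknown. But the article does not leave comparator selection to another document. It sets out the filter and the matching list, and the only step described after the filter is the match. An undefined term and unlisted covariates cannot be relied on to remove the problem.

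A reader might infer that the pool will be mostly cancer patients. The documents do not support that. The Background's statement can be read as a referral rate among non-cancer patients rather than the make-up of the pool. Nor does it describe patients who also completed advance care planning and died, or the mix after matching.

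**Conclusion.** The concern holds as a possibility that the written rule permits: non-cancer ViP patients may be matched to cancer patients, and disease may then be confounded with the programme in the utilisation, cost and concordance comparisons. The direction is open, and the documents do not allow a size to be estimated. The conclusion rests on the filter and matching list as printed, on clinical status not already covering primary diagnosis, and on the authors' own view that the disease groups differ.

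Two stronger readings go too far. One is that the question of whom ViP works for cannot be answered by disease. The subgroup analysis is optional, and 15 healthcare users per disease condition are to be interviewed, with both data streams given equal weight; only the quantitative part of that answer is weakened. The other is that limiting comparators to CGH and SACH leaves a matching share of ViP patients without a same-source comparator, since most referrals came from those two institutions, "with other organizations contributing only 7.5% of total referrals". That figure counts referrals as of May 2022, not enrolled or analysed patients, and no bias from referral source is shown.

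**What to change.** Before matching is done:

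- Exclude from the comparator pool patients whose primary condition is cancer.
- Require a primary condition in one of ViP's condition groups, as listed in the referral criteria, with an other non-cancer group so that ad-hoc admissions also have a defined comparator.
- Match exactly on primary condition group, then by propensity score within group, so that a subgroup analysis keeps its matched pairs.
- Say what clinical status contains.
- Report how many ViP patients go unmatched, by condition group.

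This needs a diagnosis filter and a change to the matching step in the same databases. The downside is a smaller pool, possibly a thin one in some groups given the low non-cancer referral that the Background reports. Some ViP patients may have no match, and the estimates would then describe the matched patients only. If the change is left until after matching, the comparator group would have to be rebuilt.
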